#### Analysis

##### Quantitative analyses.

We hypothesize that there will be no significant difference in PrU incidence between the 3 treatment arms in the study using three risk level groups: high risk (Braden Scale Score, 10–12), moderate risk (Braden Scale Score, 13–14), and low risk (Braden Scores > 14). The hypothesis of no group difference will be tested by examining whether the 95% confidence intervals of the rates of PrU and the 2-h repositioning overlap. If so, the hypothesis for no group difference will be confirmed. We will also determine how changes in medical severity components (as measured by a modified Comprehensive Severity Index), change in clinically assessed risk level (low, moderate, high as measured by the Braden Scale) and their interactions with repositioning schedule are associated with PrU development.

Descriptive statistics will be used to examine resident status, interventions, outcomes, and cost elements. For categorical variables, we will create contingency tables and use chi-squared or Fisher’s exact tests to determine the significance of bivariate differences. For continuous variables, we will use analysis of variance or non-parametric tests, depending on variable distributions. A two-sided *p*-value < 0.05 will be statistically significant. Intervention cost by NH and study arm and incremental cost-effectiveness ratios (ICERs) will be calculated and compared for cost per percentage reduction in PrUs. Sensitivity analysis will be conducted with the range of observed repositioning times, nurse salaries, and market prices for non-labor inputs to assess the robustness of the ICERs and their sensitivity to labor and non-labor input prices.

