##### Statistical power.

According to previous research, the average PrU incidence rates range from 5.2–15%. At the time of study design, the nine NHs within the NHS were identified with the highest PrU incidence rates which averaged 9.2% (SD = 3.3%). In power analyses, we used 3.5% for PrU incidence as the expected rate for intervention since it is the highest rate found in the TURN study (for moderate-risk patients). The PrU incidence rates have been translated into an odds ratio of 0.38 (= 3.5%/9.2%) as the effect size to detect. For Aim 1, odds ratios from a logistic regression of PrU incidence rates in the three treatment arms (i.e., at 2-, 3-, and 4-h repositioning frequencies), controlling for risk level, are proposed to test the difference in PrU incidence rates between the 4-h arm and the 2-h arm as well as between the 4-h arm and the 3-h arm at 4 weeks; we are assuming that the distance between the 2-h arm and the TURN 3-h odds ratio will be larger. A sample size of *N* = 951 (*n* = 317 for each arm) will be required to detect an odds ratio of .38 with a power of 0.95 at a one-tailed significance level of α = 0.05, according to G*Power. We are using a power of 0.95 instead of the conventional power of 0.80 to ensure that we will have a smaller Type II error to test the hypothesis of no-group difference that we expect to fail to reject. We are using a one-tailed test since we are only interested in determining whether the PrU rate is higher for assigned repositioning intervals longer than the current 2-h standard practice.. For Aim 2, GEE is proposed. A sample size of *n* = 114 for each group (total *N* = 342) will be required to detect an effect size of 5.7% (= 9.2% - 3.5%) with a power of 0.80 at a one-tailed significance level of α = 0.05, using the algorithms GEESIZE developed by Dahmen, et al., on an autoregressive structure for residual correlations [48]. Since the nine NHs will be randomly assigned to the three treatment arms, risk level will be the only potential covariate to be controlled in the models, and this is already considered in the power analyses. Therefore, we will target a sample size of *N* = 951 (the larger of the two required sample sizes) for both aims while taking into account potential losses due to turnover, attrition, and exclusion criteria. While this proposed study may look like a non-inferiority or equivalence trial, we will run regular one-tailed superiority tests, because (as noted earlier) we are only interested in examining whether or not the PrU rate is higher for less frequent repositioning than for the standard 2-h repositioning. (We assume that 2-h repositioning was followed to produce the 9.2% average PrU incidence rate across our 9 study NHs, because that is the current standard of care). Also, according to Snapinn [49], non-inferiority trials have many controversial assumptions and limitations that need to be made or addressed, and that is beyond the control of our study. For incidence, it is difficult to specify a non-inferiority margin for PrU rates. Instead, we will test the hypothesis of no group-difference by examining whether the 95% confidence intervals of the odds ratios (for Aim 1) or the PrU rates (for Aim 2) of the two pairs of compared groups (e.g., 4-h arm vs. 2-h arm and 4-h arm vs. 3-h arm) overlap. If the confidence intervals do overlap, the hypothesis for no-group difference will be confirmed.

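### Aim 1 has conflicting decision rules: a one-tailed 0.05 test, a 95% interval-overlap rule that confirms no difference, and a two-sided 0.05 threshold whose scope is not limited

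*Protocol article*

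**What the plan says.** The protocol article gives three rules that bear on Aim 1.

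- **One-tailed test.** Statistical power sizes Aim 1 "at a one-tailed significance level of α = 0.05, according to G*Power" and gives the reason: "We are using a one-tailed test since we are only interested in determining whether the PrU rate is higher" when the interval is longer than 2 h. It then commits to this as the analysis: "we will run regular one-tailed superiority tests". The contrasts are "between the 4-h arm and the 2-h arm as well as between the 4-h arm and the 3-h arm at 4 weeks".
- **Interval overlap.** Quantitative analyses tests the no-difference hypothesis by "examining whether the 95% confidence intervals of the rates of PrU and the 2-h repositioning overlap". Statistical power repeats the idea, for odds ratios under Aim 1 and for rates under Aim 2, and concludes: "If the confidence intervals do overlap, the hypothesis for no-group difference will be confirmed".
- **Two-sided threshold.** Quantitative analyses also states: "A two-sided *p*-value < 0.05 will be statistically significant". The sentence follows the chi-squared, Fisher and analysis-of-variance text in a paragraph on descriptive statistics. Outcomes are on that paragraph's list, and nothing confines the threshold to bivariate tables.

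Neither section says which rule prevails when they disagree.

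**The concern.** The three rules have different error rates, so one set of data can yield different Aim 1 conclusions. The sharpest conflict is between the one-tailed test and the overlap rule. Two separate 95% intervals can overlap well after a direct test of the difference has become significant. A result that the one-tailed test reads as more ulcers at 4 h can then be reported as confirming no difference.

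The error that matters here is missing harm from a longer interval, because the investigators expect no difference and want the result to inform prevention guidelines. The article justifies power of 0.95 by the wish for a small Type II error. The overlap rule works against that aim, and its errors fall toward the expected conclusion. The two-sided threshold is a smaller conflict, but it lets an arm-by-ulcer table be judged by a different standard from the Aim 1 model.

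**Working it through.** **Inputs.** From Statistical power: 951 residents, 317 per arm, odds ratio 0.38, rates 9.2% and 3.5%, one-tailed 0.05, power 0.95. From Quantitative analyses: two-sided 0.05 and 95% intervals of rates. Assumptions: no facility clustering throughout; in step 1, one third of residents in the exposed group, since the article gives no share.

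**1. The plan's own figure.** A Wald formula for logistic regression with a binary covariate is N = (z_α + z_power)² × V / (ln OR)², with V = 1/[(1−B)P1(1−P1)] + 1/[B·P2(1−P2)]. Take P1 = 0.035, OR = 1/0.38 (so P2 = 0.087) and B = 1/3. Then V = 82.1 and ln OR = 0.968.

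- One-tailed: (1.645 + 1.645)² × 82.1 / 0.968² ≈ 950.
- Two-sided: (1.960 + 1.645)² × 82.1 / 0.968² ≈ 1140.

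A Hsieh-type formula (base rate 9.2%, OR 0.38, same share) gives 964 and 1171. At power 0.95 the stated 951 therefore agrees with the one-tailed calculation and not with the two-sided one. At N = 951 the two-sided power on these formulas is about 0.90 to 0.91.

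**2. The same data under each rule.** Put 29 cases of 317 in the 2-h arm (9.1%, near the planning rate). Its Wald 95% interval is 5.97% to 12.32%. The test is the pooled two-proportion z.

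| Cases at 4 h | Rate | z | One-tailed p | Two-sided p | 95% interval at 4 h | Overlaps 2 h? |
|---|---|---|---|---|---|---|
| 43 | 13.6% | 1.75 | 0.040 | 0.080 | 9.80–17.33% | yes |
| 44 | 13.9% | 1.87 | 0.031 | 0.062 | 10.07–17.69% | yes |
| 45 | 14.2% | 1.98 | 0.024 | 0.048 | 10.35–18.04% | yes |
| 51 | 16.1% | 2.63 | 0.004 | 0.009 | 12.04–20.13% | yes |
| 52 | 16.4% | 2.74 | 0.003 | 0.006 | 12.33–20.48% | no |

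At 43 and 44 cases the one-tailed and two-sided rules disagree. From 45 to 51 both call the 4-h arm worse, yet overlap would confirm no difference.

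**3. Power for one contrast.** Use 317 per arm and 9.2% against 3.5%, with the higher rate placed in the longer-interval arm. The difference is d = 0.057. The pooled SE is 0.01937 and the unpooled SE 0.01924; the single-arm SEs are 0.01623 and 0.01032.

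- One-tailed 0.05: Φ[(0.057 − 1.645 × 0.01937)/0.01924] = Φ(1.31) = 0.90.
- Two-sided 0.05: Φ[(0.057 − 1.960 × 0.01937)/0.01924] = Φ(0.99) = 0.84.
- Non-overlap of rate intervals: d must exceed 1.960 × (0.01623 + 0.01032) = 0.0520, so Φ[(0.057 − 0.0520)/0.01924] = Φ(0.26) = 0.60.

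**4. False-positive rate toward harm.** It is 0.05 one-tailed and 0.025 under the two-sided rule. With equal standard errors, non-overlap needs z > 1.960 × 2/√2 = 2.77, a one-tailed rate of about 0.003.

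**The case against.** The strongest reply is that the two-sided sentence was never meant for Aim 1. It closes a paragraph that opens with descriptive statistics and is followed at once by costs. The Aim 1 hypothesis stands in the paragraph before it with its own rule, and Statistical power gives the Aim 1 contrasts an explicit, reasoned one-tailed test. This is probably the intended reading, and it stands. A reader might infer that the article sets two flatly opposed alpha levels for the primary test; the text does not support that. What remains is a missing limiting phrase, which matters because outcomes are among the variables in that paragraph. Sidedness alone affects only one-tailed p between 0.025 and 0.05, which is two case counts in the example.

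A reader might also infer that the analysts are free to choose among three rules after seeing the data. That is too strong: both sections consistently name overlap as the way to judge no difference. This does not remove the conflict, because the article also commits to the one-tailed test and sizes the trial on it.

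Three limits on the figures are fair.

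- Statistical power attributes 9.2% to 2-h care and 3.5% to the intervention. In that arrangement a one-tailed test for a higher rate at longer intervals has essentially no power, so the figures in step 3 describe harm detection only with the rates swapped.
- The 0.90 for a single contrast is not the stated 0.95, which is approached only by the total-N logistic formulas with an assumed share. The comparison across rules is the point here, and it does not show that 951 was miscalculated.
- The 0.60 uses intervals of rates, as in Quantitative analyses. Statistical power speaks of odds ratios for Aim 1; intervals of each arm's log odds give about 0.55, so the direction is the same.

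**Conclusion.** The concern holds in this form: the one-tailed test and the overlap rule, both stated for Aim 1, can return opposite conclusions, and an unrestricted two-sided threshold adds a lesser ambiguity. In the example, 45 to 51 cases at 4 h against 29 at 2 h is a harm signal under either p-value and a confirmed null under overlap. The power stated for the one-tailed test does not carry over to the other rules: for the planning difference taken as harm, it falls from about 0.90 to 0.84 two-sided and 0.60 under non-overlap.

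These sizes rest on 317 per arm, independent residents, Wald intervals of rates and the higher rate in the longer-interval arm. With nine facilities, clustering would change the counts, p-values and error rates, but not the fact that the rules disagree.

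**What to change.** - In Quantitative analyses, limit the two-sided 0.05 threshold to descriptive and bivariate comparisons.
- State one Aim 1 rule in both sections: the one-tailed 0.05 test of the odds ratio for 4 h v 2 h and for 4 h v 3 h, each reported with its matching 90% confidence interval.
- Delete the interval-overlap rule from both sections, together with the statement that overlap confirms no difference. The sentence in Statistical power also covers Aim 2, so its deletion applies there too.
- Report a non-significant result as no difference shown, with its interval, so that the reader sees which increases in ulcer incidence remain compatible with the data.
- If two-sided 0.05 is preferred for Aim 1, use it throughout and restate the power: about 0.84 for one contrast under the assumptions above, or about 1140 to 1171 residents to keep 0.95 on the formulas in step 1.

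The cost is a wording change, plus a lower stated power if the two-sided option is taken. No new data are needed. The article reports three of nine homes already completed, so the change should be made and dated before outcomes are analysed by arm.

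### Overlap of 95% confidence intervals is taken to confirm no group difference, although overlap neither tests the difference nor shows equivalence and can contradict the plan's own one-tailed test

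*Protocol article*

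**What the plan says.** The rule appears twice in the protocol article's Analysis section.

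- Under Quantitative analyses, the assumption that the arms do not differ "will be tested by examining whether the 95% confidence intervals of the rates of PrU and the 2-h repositioning overlap", and overlap is taken to confirm it.
- Under Statistical power, the check consists of "examining whether the 95% confidence intervals of the odds ratios (for Aim 1) or the PrU rates (for Aim 2) of the two pairs", a pair being two arms under comparison, and the text concludes: "If the confidence intervals do overlap, the hypothesis for no-group difference will be confirmed".

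The second statement is offered in place of a non-inferiority margin, which the authors say is hard to specify for ulcer rates. The same section commits to ordinary one-tailed superiority tests of whether the rate is higher at longer intervals. It sizes the trial at "317 for each arm", "with a power of 0.95 at a one-tailed significance level of" 0.05, and explains the high power as protection against a Type II error on a null hypothesis that the authors expect not to reject. Facility-clustered standard errors are specified under Quantitative analyses. No intracluster correlation (ICC) is given.

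**The concern.** The trial asks whether repositioning can be spaced out without raising ulcer incidence, so the error that matters most is declaring a longer interval safe when it is not. The overlap rule is weak against that error in three ways.

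- Two 95% intervals can overlap while the difference between the arms is clearly significant.
- Overlap shows only that the data did not separate the arms. Fewer residents or stronger clustering widen the intervals and make confirmation more likely, so imprecision counts in favour of safety.
- The article fixes two decision rules, overlap and a one-tailed test. They can give opposite answers on the same data, and it does not say which prevails.

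The Discussion in the abstract says that the results will contribute to prevention guidelines, so a false confirmation could reach practice.

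**Working it through.** **Inputs from the article.** 317 per arm; one-tailed alpha 0.05; power 0.95; 3.5% as the expected rate under intervention; 9.2% assumed to reflect 2-h care ("the nine NHs within the NHS were identified with the highest PrU incidence rates which averaged 9.2% (SD = 3.3"%); earlier rates from 5.2%; 3 homes per arm, so about 106 residents per home.

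**The plan's own figure.** The Wald sample size for logistic regression with a binary predictor is N = (z₀.₉₅ + z₀.₉₅)² × V / (ln OR)², with V = 1/[(1−B)p₁(1−p₁)] + 1/[B p₂(1−p₂)]. With p₁ = 3.5%, OR = 1/0.38 = 2.63 (so p₂ = 8.7%) and B = 1/3, V = 82.1 and N = 10.82 × 82.1 / 0.935 = 951. The base rate and the one-third split are inferred. The figure is thus reproduced as a total, not as 317 against 317. For that pairwise comparison (3.5% versus 9.2%) the one-sided power is about 0.90 to 0.92 before clustering.

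**What non-overlap amounts to.** For two arms with similar standard errors, two 95% intervals separate only when |z| exceeds 1.96 × √2 = 2.77, a two-sided level of about 0.006. With equal true rates, an exact calculation gives non-overlap about 0.4% to 0.5% of the time.

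**Probability of overlap.** The unclustered column sums exactly over both binomial distributions at 317 per arm with Wilson intervals. The clustered columns use 3 × 106 residents per arm and intervals widened by the design effect 1 + 105 × ICC. The ICCs are assumptions, and the ranges span two sets of calculations that differ in method.

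| True rates | Independent | ICC 0.005 | ICC 0.01 |
|---|---|---|---|
| 3.5% vs 7% | 80% | 86–89% | 90–93% |
| 5.2% vs 10.4% | 63% | 77–80% | 84–87% |
| 9.2% vs 18.4% | 27% | 50–52% | 64–67% |
| 3.5% vs 9.2% | 42% | 61–65% | 72–78% |

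Across other interval methods the independent figures run 77–84%, 61–68%, 26–31% and 40–48%.

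**Plausible ICC.** The spread of 3.3 points between homes caps it at 0.033² / (0.092 × 0.908) = 0.013. Subtracting binomial noise for an assumed 100 to 150 residents per home leaves about 0.003 to 0.006.

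**Conflict with the superiority test.** At 3.5% versus 9.2%, with the longer interval as the worse arm and independent residents, the one-tailed test is significant in about 92% of trials. In about 34% of all trials it is significant and the intervals still overlap. Example: 11/317 (3.5%) versus 24/317 (7.6%).
- Pooled rate 35/634 = 5.52%; SE = √(0.0552 × 0.9448 × 2/317) = 1.81 points; z = 4.10/1.81 = 2.26; one-sided p = 0.012. Doubled, this is 0.024.
- Wilson intervals are 2.0–6.1% and 5.1–11.0%, which overlap.

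The test reports a higher rate and the overlap rule confirms no difference.

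**The Aim 1 wording.** The article refers to odds-ratio intervals "of the two pairs of compared groups (e.g., 4-h arm vs. 2-h arm and 4-h arm vs. 3-h arm) overlap". If the 4-h versus 2-h interval is compared with the 4-h versus 3-h interval, both share the 4-h arm. In simulation with 2-h and 3-h at 3.5% and 4-h at 7%, 9.2% or 15%, they overlap more than 99.9% of the time. If 3-h shares the harm, overlap is lower: about 64% with 2-h at 9.2% and both longer intervals at 18.4%.

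**The case against.** Several points on the other side are fair.

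- A reader might infer that the rule will usually pass a doubling of the ulcer rate. The documents do not support that without a condition. It holds from 3.5% and 5.2%. From 9.2%, which the plan attaches to 2-h care, overlap is 27% with independent residents and reaches about half only at an assumed ICC near 0.005.
- A reader might infer that the trial cannot detect harm. It can: one-tailed superiority tests are planned, with about 92% power at 3.5% versus 9.2% before clustering. What stands is that the overlap rule can overturn their result.
- A reader might take the blindness of the Aim 1 form as settled. The wording can also mean overlap within each pair of arms, and the Quantitative analyses section, which refers to the 2-h arm, fits that better. The near-certain overlap belongs to one reading only.
- The authors considered a non-inferiority design and declined it. That is their choice, but lacking a margin is a reason not to claim equivalence. It does not make overlap a substitute.

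None of this rescues the rule, which is stated twice and softened nowhere in the article.

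**Conclusion.** The rule is wrong as written and must be changed. At the plan's own contrast it would confirm no difference about 42% of the time (40–48% across interval methods), against the 5% that power of 0.95 implies. For a doubling, the figure runs from 80% at a 3.5% base to 27% at a 9.2% base. These figures assume 317 independent residents per arm. Clustered intervals raise them, by an amount that depends on an ICC the article does not give. The internal conflict does not depend on the base rate: significant harm and confirmed equality can be declared from the same data.

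**What to change.** Delete the overlap rule under both Quantitative analyses and Statistical power, and replace it as follows.

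1. Base conclusions on the facility-adjusted difference in 4-week incidence (or the odds ratio) for 4-h versus 2-h and 3-h versus 2-h, each with its confidence interval.
2. Report a significant one-tailed result as a higher rate. Report a non-significant one as inconclusive, with its interval, and never as confirmation of no difference.
3. Claim that an interval is not worse only if the upper confidence limit lies below a maximum increase that the sponsor states and justifies in advance. The 5.7 points in the power section should not serve by default. It is an effect size to detect, and from 3.5% it would allow 9.2%, a 2.6-fold rise. With that margin, a true doubling from 3.5% would still pass about 36% of the time before clustering.

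No new data are needed. The cost is that the trial may end inconclusive. If the home-level SD of 3.3 points applies during the intervention, the standard error of a difference between two arms of 3 homes is 3.3 × √(2/3) = 2.7 points. With t on 6 degrees of freedom (1.94), the one-sided 95% limit lies about 5.2 points above the estimate.

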
##### Missing data.

When data are missing, we will make adjustments depending on the variable and its intended use in the analyses. Residents with missing data will be deleted from analyses and continuous variables with missing data collapsed into categorical data, and cases with missing information for the continuous variable placed into a category using corroborating data. For example, we may not always have a resident’s body mass index, but may have other weight- and height-related information (e.g., resident description as ‘emaciated’) that allows us to categorize a resident broadly, e.g., as underweight. We will use various types of imputation as appropriate and check assumptions about ‘missing at random’. To exclude unrealistic values and obvious outliers from the analysis, we will set ranges for some variables, and values beyond those ranges will be deemed improbable and excluded. These values may also be sent back to the NHs for correction.

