#### Resident sample

All residents (≥ 18 years old) using a VE mattress (support surface) who are without PrUs and adhesive allergy and are clinically assessed as low, moderate, or high risk for new PrU development will participate in their respective NH-wide repositioning frequency protocol and receive standard PrU prevention care.

NH resident participants will include those residents at the time of study initiation and any residents newly admitted during the 4-week study period. All individuals who are NH residents for a minimum of 3 days and meet inclusion criteria will be included in data analyses, because superficial PrUs have been reported to occur within several hours to days following NH admission, and “deep tissue injury”, a type of PrU resulting from pressure on muscle and fascia is thought to appear on the surface of the skin approximately 3 days following exposure to pressure.

A waiver of informed consent has been obtained from the Primary Investigator’s (PI) Institutional Review Board. Data on newly admitted residents with less than a 3-day stay will not be included in the analysis, because deep tissue injuries that result from pressure prior to admission may not be visible for up to 3 days after pressure exposure. Residents will also be excluded from the analysis if PrUs are present at baseline, PrU risk is severe (Braden score ≤ 9), or if the resident is cared for on a non-VE specialty surface, has “do not turn orders” present, or has an allergy to the adhesive used on the sensor. Residents assessed as being at severe risk of developing a PrU (estimated ≤ 10% per NH) will be excluded because they typically require specialty surfaces and individualized and frequent repositioning, and their health status is generally more unstable. Data on all other residents will be included, using an intention-to-treat approach. The target N for analysis is 951; we aim to enroll 1100 residents at baseline. Residents who are discharged, transferred, or die will be included in the intention-to-treat analysis.

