Because we will be examining PrU development from assessment to assessment, the rate of PrU incidence will be modeled as a binary outcome using repeated measures logistic regression and a specified working correlation matrix that models the correlation of responses within subjects. Full likelihood estimation methods are not appropriate for repeated measures logistic regression, so generalized estimating equations (GEEs) will be used instead with model fit assessed using the quasi-likelihood information criterion (QIC). Robust standard errors, clustered at the facility level, will be employed to account for covariance among residents within facilities over time. To test the robustness of models, we will also use non-linear mixed models using PROC GLIMMIX as another option for modeling the data (instead of GEEs using PROC GENMOD). With PROC GLIMMIX, we can use random effects to model the covariance rather than clustered standard errors. As predictors, we will include time-invariant resident characteristics, e.g., age, gender, Medicaid payer, and repositioning schedule, as well as time-varying characteristics, such as resident severity measure, risk level as determined by Braden Scale© score, staffing characteristics (e.g., number, mix, and turnover), and suggested MDS resident data elements as covariates. We may lag some time-varying resident characteristics by one assessment because we want to study the associations of repositioning time with PrU development, controlling for the starting point of the resident for that assessment interval. Interaction variables will be included in the predictor data set.

Residents without PrUs who drop out of the study after at least a three-day stay but before the conclusion of 4 weeks will be included in the analysis based on intent to treat. Residents who develop a Stage 3 or worse PrU, or deep purple discoloration, will be removed from the study per repositioning protocol, but will be considered a completed case if the ulcer developed on the coccyx, sacrum, trochanter or heel. Residents who develop ulcers on sites not thought to be influenced by bed position or limited mobility, or related to sitting, will continue to be followed for analysis, but will not be included in the NH-wide protocol.

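### The missing-data section's unrestricted deletion of residents contradicts the intention-to-treat analysis and sits unreconciled beside categorisation and imputation

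*Protocol article*

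**What the plan says.** The Missing data section opens with a general principle: "When data are missing, we will make adjustments depending on the variable and its intended use in the analyses". It then names three treatments.

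- **Deletion:** "Residents with missing data will be deleted from analyses and continuous variables with missing data collapsed into categorical data".
- **Categorisation**, later in the same sentence: "cases with missing information for the continuous variable placed into a category using corroborating data". The example is body mass index, where a description of the resident can stand in for the number.
- **Imputation:** "We will use various types of imputation as appropriate and check assumptions about" missingness at random.

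The section also sets plausibility ranges, and "values beyond those ranges will be deemed improbable and excluded", which creates further missing values unless the nursing home corrects them.

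The analysis population is defined elsewhere. After its list of exclusions, the Resident sample section says: "Data on all other residents will be included, using an intention-to-treat approach". It adds: "Residents who are discharged, transferred, or die will be included in the intention-to-treat analysis". Under Quantitative analyses, residents without an ulcer who leave after at least three days "will be included in the analysis based on intent to treat".

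**The concern.** The deletion clause is not limited to a variable, a model or an aim. Taken at its word, it removes any resident with a gap, and it removes the whole resident, not just the assessment at which the gap occurs. The Resident sample section does not allow that. The three treatments also compete: a resident who lacks one covariate could be deleted, categorised or imputed, and each choice gives a different analysis set. The opening sentence says that the choice will vary but does not make it.

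Two things are at stake. The first is precision. The Statistical power section treats overlapping confidence intervals as confirming no difference, so any loss of precision pushes towards the result that the investigators expect. The second is bias, which arises if residents with missing data differ in ulcer incidence from the rest.

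**Working it through.** **1. The texts side by side.** The Resident sample section excludes these residents from analysis: new admissions staying under 3 days, ulcer at baseline, Braden score of 9 or less, non-VE specialty surface, do-not-turn order, and adhesive allergy. Everyone else is in. Missing data is not on the list, so unrestricted deletion is a seventh exclusion. The Statistical power section does not allow for it by name either: the losses it mentions are turnover, attrition and exclusion criteria. The margin from 1100 enrolled to 951 analysed is 149/1100 = 13.5%.

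**2. Where deletion would act.** Table 2 defines cumulative incidence over residents with 3 or more days of participation, so an early leaver still counts and has no missing outcome on that definition. Deletion therefore works mainly through covariates. The Statistical power section describes Aim 1 as logistic regression controlling for risk level only. Quantitative analyses lists far more for the GEE models: demographics, payer, severity, Braden level, staffing and MDS items, several of them time-varying and possibly lagged.

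**3. Size for a lean Aim 1 model.** The plan gives no missing-data figure to reproduce. Assume that 3% lack a risk level: 951 × 0.97 = 922, or 307 per arm. Take 9.2% v 3.5% (Statistical power section), one-sided 0.05, clustering ignored, mean rate 0.0635:

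power = Φ{[0.057 − 1.645·√(2·0.0635·0.9365/n)] / √[(0.092·0.908 + 0.035·0.965)/n]}

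- n = 317: (0.057 − 0.0319)/0.0192 = 1.31, power 0.904
- n = 307: (0.057 − 0.0324)/0.0195 = 1.26, power 0.896

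The loss is under one percentage point. (The plan's 0.95 does not come out for a pairwise contrast at 317 per arm. That is a separate matter; only the change counts here.)

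**4. Size for a model with many covariates.** Assume k resident-level covariates, each missing in a share r. If gaps are independent, the deleted share is 1 − (1 − r)^k. If the same residents lack everything, it is only r.

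| k | r | Deleted, complete overlap | Deleted, independent | Left of 951 |
|---|---|---|---|---|
| 5 | 2% | 2% | 10% | 932 to 860 |
| 10 | 3% | 3% | 26% | 922 to 701 |
| 15 | 3% | 3% | 37% | 922 to 602 |

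The range is wide, and the protocol gives nothing to narrow it.

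**5. Bias.** Delete a share d1 of residents with an ulcer and d0 of those without. The observed rate is p(1 − d1)/[p(1 − d1) + (1 − p)(1 − d0)].

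- p = 9.2%, d1 = d0 = 10%: 9.2%, no bias.
- p = 9.2%, d1 = 20%, d0 = 10%: 8.3%.
- p = 9.2%, d1 = 30%, d0 = 10%: 7.3%.

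If both arms lose residents in the same way, the odds ratio does not change, because (1 − d1)/(1 − d0) cancels, but the rates move: at 20% and 10%, 9.2% v 3.5% becomes 8.3% v 3.1%. If only one of two arms with equal true rates loses 20% and 10%, while the other loses 10% and 10%, the odds ratio becomes 0.8/0.9 = 0.89 instead of 1. All these shares are assumptions.

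**The case against.** The strongest reply is that deletion is not the section's only rule. It opens by tying the treatment to the variable, the deletion clause runs straight into one that retains cases, and imputation with a check on missingness at random follows. Assigning methods to variables is commonly left to the analysis plan, which is not shown. This stands in part: silence on the assignment alone would be no finding. But the deletion clause is a stated rule without limits, and it conflicts with the stated population.

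A second reply also has force. The intention-to-treat statements mainly concern discharge, transfer, death and dropout, and early leavers remain in the incidence denominator. That confines the effect largely to covariate-adjusted models. It does not remove the conflict, because the Resident sample statement covers all residents not excluded, whatever the reason their data are incomplete.

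On precision, the plan's own Aim 2 calculation asks for 342 residents, and even the worst row in the table leaves 602. That calculation addresses a 5.7-point difference, not the interactions that Aim 2 also studies, so it is only partial reassurance.

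A reader might go further in three ways that the protocol does not support:

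- **Selective removal.** It is plausible that residents who die, transfer or leave early have thinner records and a different ulcer risk. The protocol reports neither.
- **Large loss of Aim 1 power.** Deletion of 10% to 37% needs 5 to 15 covariates with independent gaps. Aim 1 is described with one covariate, which is also needed for eligibility. If gaps cluster in the same residents, the loss is smaller still.
- **Categorisation as a fault.** Here its purpose is to keep cases, so it is no part of this point.

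**Conclusion.** The contradiction is certain: unrestricted deletion cannot stand with an intention-to-treat analysis of all residents outside the listed exclusions, nor with categorisation and imputation of the same missing values. Its consequences are conditional. In the GEE models, precision would fall by an amount that cannot be fixed from the protocol. The arm comparison could be biased if missingness is related to outcome; on the odds-ratio scale of the simple two-arm illustration, that relation must also differ between arms. For an Aim 1 model with arm and risk level only, the loss is probably small. The figures above rest on assumed missing-data rates and ignore clustering. The clause should be changed, because following it would give a worse analysis set and changing it is cheap.

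**What to change.** - Strike the deletion clause from the Missing data section.
- State that the Aim 1 model (arm, baseline risk level, outcome) keeps all eligible residents.
- In the covariate-adjusted models, handle missing covariates by multiple imputation that includes facility, arm and outcome, with corroborating data used where available.
- Treat values set aside as out of range in the same way when they are not corrected.
- Report complete-case results only as a sensitivity analysis.

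The cost is a change of wording and modest extra programming, with no new data collection.
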